## Abstract

**Background:**

In 2013 vocational rehabilitation programmes (VRP) were given official and legal approval under Danish law to assist occupationally marginalized citizens in gaining general life skills, building their work ability, and increasing their chances of entering the work force. The project’s aim is to develop a detailed understanding of the health, psychosocial and work circumstances of participating citizens, and of the important processes and mechanisms underlying the potential effects of participating in the VRP.

**Methods:**

This study uses an exploratory mixed methods approach with sequential use of quantitative and qualitative methods. Participants are citizens assigned to an individually tailored VRP in the municipality of Sonderborg, Denmark. The quantitative part of the study consists of a longitudinal survey in which participants complete questionnaires at baseline and at follow-up one year later. Variables include demographic and personal characteristics, the latter ascertained through validated questionnaires on well-being, physical activity, interpersonal problems, general health, work ability, kinesiophobia, self-efficacy, depression and anxiety. The qualitative part of the study consists of semi-structured interviews and observations that explore experiences related to VRP. Participants will be recruited and data collected from questionnaires, interviews and observations in the period February 2016 – March 2018.

**Discussion:**

This research will assemble a unique corpus of knowledge about the characteristics, experiences and outcomes of occupationally marginalized citizens participating in a VRP. It will identify potential enablers and barriers to a successful outcome, and ultimately this knowledge will help inform the future design of individually tailored VRP’s.

**Trial registration:**

ClinicalTrials.gov Identifier: NCT02641704, date of registration December 29, 2015.

## Background

Vocational rehabilitation for those situated on the margins of the work force is a challenge in most Western societies. For example, although the majority wish to work [1], international studies show that as few as 15% of people with severe mental health problems hold gainful employment [2, 3]. In Sweden, almost half of participants on various vocational rehabilitation programmes have ended up with a disability pension [4]. This strongly belies the notion that labour participation is an important element in recovery, regardless of the reason for unemployment or the individual’s underlying condition, and that work is closely linked with better quality of life [5, 6].

The challenge of obtaining and retaining a job has only rarely been evaluated for various groups of marginalized citizens. For people with severe mental illness, a recent meta-analysis has shown that vocational employment, individually designed and supported, is an effective avenue to employment [7]. For example, the positive findings of several individual placement and support studies [8, 9], which consider competitive employment as the only outcome of interest, have promoted further discussions of the way vocational rehabilitation is offered. Evidence also supports the positive effects on employment of information being exchanged between stakeholders from the healthcare sector and work place [10]. Therefore, there is a need for more research that can tie interventions related to health and employment closer together [11, 12]. In addition, more research is needed on the role of rehabilitation professionals and on their willingness to collaborate with relevant key stakeholders, such as vulnerable citizens and their employers [13].

In Denmark, vocational rehabilitation programmes (VRP) are provided by the local authorities (municipalities) and set within the tax funded social service system. They are designed to assist vulnerable, unemployed, and occupationally marginalized individuals in a structured manner, the objective being to increase their chances to entering the work force. To this end the programmes providing general life and social skills and build up work ability through individually tailored, holistic interventions. Citizens eligible for VRP are defined as those struggling over prolonged periods of time, often years, with multiple and/or significant issues, including physical health problems, mental disorders and/or social issues, which render them vulnerable and marginalized. They are potential candidates for early retirement benefits, but these can only be approved, if a VRP of between one and five years has not been successful [14].

The VRP’s are therefore individually tailored programmes designed to help citizens develop their personal skills that will increase their chances of entering the work force.

The programme were officially ratified by the Danish Government in 2013 [15]. A Danish report [16] showed that 90% of participants in VRP’s had occupational experience, 95% of the participants already receive government benefits, out of which 60% receive sickness absence benefits. The report also stated that conditions related to health, both physical and mental, are very often barriers to employment, further education or re-training [16]. Despite this report, there is still significant lack of knowledge about the personal characteristics and profiles of citizens assigned to VRP, including their everyday life situations and of their mental and physical health conditions, and, ultimately, about the impact on individuals and the outcomes of the VRP.

This paper describes the design of an exploratory mixed methods study, which based on studies in the social service sector in Denmark, will contribute knowledge about occupationally marginalized citizens and their participation in VRP’s.

### Research aim and objectives

The aim of this study is to develop a detailed understanding of citizens assigned to an interdisciplinary VRP in one municipality in Denmark, covering their health, their psychosocial and work situation, and significant processes and mechanisms underlying the potential effects of participating in VRP.

The objectives are :to develop a descriptive profile of the citizens assigned to a VRP in Sonderborg Municipalityto obtain an understanding of the potential developmental path citizens take when participating in a VRPto examine how citizens experience the impact of the VRPto explore the role of social interactions on the citizens’ path of development.

## Methods/design

### Study design

A mixed-method exploratory approach [17] with the combined use of quantitative and qualitative methods will be used in this study, because the research objectives are complex and comprehensive in nature and they require multiple outcomes. A range of data will need to be assembled and analysed to provide a sufficiently nuanced picture if the project is to achieve its objectives. This combined methodological approach uses a variety of data collection methods. These will be described in part A and part B below.

### Participants

Eligible participants are assigned to a VRP in Sonderborg Municipality. Criteria for acceptance on a VRP are as follows: a) Participants should be unemployed citizens aged 18 to 65 years, b) They have been assessed as being vulnerable and occupationally marginalized because of complex challenges around one or more issues, such as social problems, physical conditions or mental disorders, c) The complex nature of their problems and their situation means that they are not directly available for the labour market, candidates for continued education or retraining of skills, and d) They are at high risk of early retirement.

### Study settings

Towards the end of 2015, in accordance with Danish legislation on VRP, Sonderborg Municipality in the southern part of Denmark (population approximately 75,000) established a *Competency and Integration Center (CIC)* within the social services department. The CIC initiates and coordinates VRP’s based on an expected enrolment of approximately 400 citizens per year. The VRP’s offered by Sonderborg Municipality are individually tailored, multifaceted programmes, which are designed so they can contain different types of intervention related to employment, health and the management of everyday life.

Because the content of the VRP’s is tailored to the individual citizens, the local Health Care Centre as well as local educational institutions and companies may be involved in executing elements of VRP in collaboration with the CIC.

### Vocational rehabilitation program

#### Eligibility for inclusion in VRP

Citizens’ eligibility for the VRP is determined by a social worker at the Job Center. In cooperation with the citizen, the social worker submits an application for the citizen to be included in a VRP programme. The application is sent to an interdisciplinary rehabilitation team in the municipality with an individual, targeted plan for rehabilitation. This plan is discussed at a meeting with the citizen, the social worker and the rehabilitation team, and the rehabilitation team may suggest alternatives. The rehabilitation team makes a final decision about granting a VRP only after consultation and dialogue with the citizen. The process is described in Fig. 1.

**Fig. 1 Fig1:**

Timeline for participation in VRP in sonderborg municipality

#### Programme content

Each citizen in the programme is assigned a coordinative social worker. Throughout the course of the programme, the social worker assists the citizen in tailoring and carrying out the programme. The programmes are individually tailored, involve a holistic view of the citizen’s situation, are interdisciplinary and aim to build up the citizens’ work ability. The following are examples of the activities that can be included in the programmes, either as a single component or in combination:Training in social skills (e.g. Leisure activities, company internship programs, voluntary work)Municipality based support services (e.g. Providing a supporting contact person and/or mentor)Courses in self-management or in supervision of issues related to mental or physical health (e.g. Chronic pain, anxiety, depression and post-traumatic stress disorder, physical activity, overweight, dietary habits or smoking)Treatment for alcohol and drug abuseRehabilitation after chronic disease (e.g. Cancer, chronic obstructive lung disease, arthritis, musculoskeletal disorders or heart diseases)Employment integration services (e.g. Internship programmes)Educational services (e.g. Supervision, school-leaving examination and supplementary education)Family therapy services

### Methods part A

This part is a longitudinal survey using postal questionnaires at baseline and at one-year follow-up.

### Inclusion of participants and time sequences

Participants will be drawn from databases containing all citizens assigned to VRP in Sonderborg Municipality. At the start of the project period, data on citizens assigned to a VRP during the previous year will be retrieved. After that, we will continue to retrieve lists with citizens assigned to the programme.

In Part A, citizens will be recruited to fill out questionnaires from February 2016 to March 2017. Follow-up questionnaires will be sent February 2017 – March 2018. A timeline for data collection is presented in Fig. 2.

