### Data collection methods for part A – Quantitative

Questionnaires will be sent via postal mail to all citizens assigned to VRP at baseline (A1) and at follow-up (A2) after one year. The questionnaire is designed to add to the descriptive profile of the participants as regards their gender, age, height, body weight and demographic characteristics, such as educational qualifications and domestic situation.

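### The A1 baseline is a study baseline taken at varying programme stages, because citizens assigned in the year before the study are surveyed together with new assignees

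*Protocol article*

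**What the plan says.** In the protocol article, under Inclusion of participants and time sequences (Methods part A), the frame is defined broadly: "Participants will be drawn from databases containing all citizens assigned to VRP in Sonderborg Municipality". It is filled in two steps. First, "At the start of the project period, data on citizens assigned to a VRP during the previous year will be retrieved". Then, "After that, we will continue to retrieve lists with citizens assigned to the programme".

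The same section sets the calendar: "In Part A, citizens will be recruited to fill out questionnaires from February 2016 to March 2017", and "Follow-up questionnaires will be sent February 2017 – March 2018". Under Data collection methods for part A, the mailing rule makes no distinction by date of assignment: "Questionnaires will be sent via postal mail to all citizens assigned to VRP at baseline (A1) and at follow-up (A2) after one year".

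Two other places matter. Study settings dates the centre that now initiates and coordinates the programmes (the CIC): "Towards the end of 2015, in accordance with Danish legislation on VRP, Sonderborg Municipality" established it. The Background indicates how long a programme can last, where it says that early retirement benefits can be approved only "if a VRP of between one and five years has not been successful".

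The text shown does not separate earlier from new assignees, and it does not mention time since assignment as a reported quantity or a model term.

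**The concern.** In a one-year longitudinal survey of people in a programme, the word baseline invites the reader to take the first measurement as status at or near entry, and the change to follow-up as what happens over the first year. Here neither reading holds for everyone. For a citizen assigned some months before the study, A1 is a mid-programme measurement, and A2 falls well into the second year after assignment.

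This bears on two stated uses of the data. The second objective (Research aim and objectives) is to understand the path citizens follow while in a programme. The Discussion expects to evaluate change in work ability and the programme's possible influence on working life. If programme stage varies at A1 and is not tracked, differences in stage are mixed into the baseline values, into the changes, and into the associations between time points planned under Data from questionnaires. Some earlier assignees also entered before the CIC existed, so the organisational setting at entry may differ too.

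**Working it through.** The plan gives no figure on this point to reproduce. The expected 150 participants (Study size, Part A) come with no power or precision calculation. The check is therefore a timeline plus an illustration under stated assumptions.

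**Timeline.** Take the start of the project period as February 2016, the first month of A1 recruitment (an assumption).

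- Earlier assignees were assigned between about February 2015 and January 2016. If surveyed promptly, A1 falls 0 to 12 months after assignment, and A2, one year later, falls at 12 to 24 months.
- New assignees were assigned from February 2016 on. If surveyed promptly, A1 falls near assignment and A2 at about 12 months.
- The CIC dates from late 2015, so part of the earlier window precedes it.
- With programmes of one to five years, many earlier assignees can still be in a programme at A1.

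The A1 to A2 interval is about 12 months for both groups. The starting point differs, not the interval.

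**Share of earlier assignees in the frame.** Inputs: 400 citizens a year (Study settings, the CIC's expected enrolment); a 14-month A1 window, February 2016 to March 2017. Assumptions: assignment is uniform over time, response is equal in both groups, and the number of earlier assignees B is 100, 200 or 400 (3, 6 or 12 months at the same rate).

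New assignees: 400/12 × 14 = 467. Share s = B/(B + 467).

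| B | s | of 150 participants |
|---|---|---|
| 100 | 17.6% | 26 |
| 200 | 30.0% | 45 |
| 400 | 46.2% | 69 |

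**Effect on pooled change.** Let f be the one-year change in earlier assignees divided by that in new assignees. Pooled change as a fraction of the new assignees' change is 1 − s × (1 − f).

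| s | f = 0 | f = 0.5 | f = 1 |
|---|---|---|---|
| 17.6% | 0.82 | 0.91 | 1.00 |
| 30.0% | 0.70 | 0.85 | 1.00 |
| 46.2% | 0.54 | 0.77 | 1.00 |

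The documents give no value for f. If change were linear for 12 months and then stopped, a full year of earlier assignees, on average 6 months in at A1, would have f = 1 − 6/12 = 0.5. If only the last 6 or 3 months were retrieved, the mean would be 3 or 1.5 months. Then f = 0.75 or 0.875, and the pooled fraction would be 1 − 0.300 × 0.25 = 0.925 or 1 − 0.176 × 0.125 = 0.978. If change continues at the same rate in the second year, f = 1 and nothing is diluted.

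**The case against.** The strongest reply is that the protocol never promises an entry-state profile or a first-year effect. The first objective is a profile of citizens assigned to a programme, and a frame of recent and earlier assignees suits it. Baseline can simply mean the first survey round. The study is exploratory and uncontrolled, everyone is followed for about one year, and regression and generalized estimating equations are planned and could take time since assignment as a term. An analysis plan that is not shown may do so, and the two timeline figures cannot be seen.

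Much of this stands. The overall profile remains usable, within-person change over a common interval can still be described, and the absence of a covariate rule from a condensed article is not itself a fault. But the article itself fixes the frame and the mailing rule, and these leave A1 without a common position in the programme. No later analysis can recover a pre-programme measurement for people already assigned, and the Discussion does intend to speak of change and influence.

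Three stronger readings are tempting but unsupported:

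- **A definite dilution, such as 77% to 91% of the first-year change.** This needs an assumed group size and an assumed f. The 400 is the expected enrolment of a centre that did not exist for most of the earlier year.
- **Under-representation of early leavers.** The frame is everyone assigned, not those still active. Differential non-response is possible but undocumented.
- **Pooled results that describe nothing useful.** They describe assigned citizens at mixed stages, which is consistent with the first objective.

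Two further limits apply. That earlier assignees receive A1 is inferred from the two sections read together, although no other use of the retrieved data is given. Assignment may also precede actual start, so exposure at A1 could be shorter than the time since assignment.

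**Conclusion.** The point holds as a problem of time origin. The protocol implies that one questionnaire, called baseline, is answered by new assignees and by people assigned up to about a year before the study. A1 values and A1 to A2 changes therefore mix programme stages, which weakens the developmental-path objective and the intended reading of programme influence. It does not invalidate the overall profile of assigned citizens.

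The size is uncertain. The earlier group is about 18% to 46% of the frame (about 26 to 69 of 150) if there are 100 to 400 earlier assignees, new assignments run at 400 a year and response is equal. With f between 0 and 1, the pooled change lies between 54% and 100% of the new assignees' change. Neither range is a figure from the documents. The point is worth correcting because the correction is nearly free and becomes impossible if assignment dates are not kept.

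**What to change.** 1. Take the assignment date, and the programme start date if available, from the municipal lists already being retrieved, and keep it with the survey data.
2. State that A1 is the study baseline, not programme entry, and report the distribution of time from assignment to A1.
3. Present the baseline profile and the A1 to A2 change separately for recent and earlier assignees, with the dividing line set before the data are examined. Assignment before or after the start of the project period is a natural choice.
4. Include time since assignment, or an earlier/new indicator, in the planned regression and generalized estimating equation models.
5. Limit statements about entry status or first-year change to recent assignees. Keep all participants in the overall profile of assigned citizens.

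The cost is one or two date fields and a few sentences in the methods. The real downside is lower precision for recent assignees: 150 − 26 = 124 to 150 − 69 = 81 participants in the illustration, so standard errors would be about √(150/124) = 1.10 to √(150/81) = 1.36 times those for all 150. For that reason the main sample should not be cut to a narrow window after assignment; separate reporting is enough.

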**Fig. 2 Fig2:**
[figure not shown]
Timeline for data collection

### Data collection methods for part A – Quantitative

Questionnaires will be sent via postal mail to all citizens assigned to VRP at baseline (A1) and at follow-up (A2) after one year. The questionnaire is designed to add to the descriptive profile of the participants as regards their gender, age, height, body weight and demographic characteristics, such as educational qualifications and domestic situation.

#### The physical domain

*Work ability* will be measured using a single question from the Work Ability Index [18] “Imagine that your work ability is worth 10 points when it is at its best. How many points would you give your present work ability?”. The answer will be recorded on an 11-point numeric rating scale from zero to ten, where zero represents ‘not able to work’ and ten ‘highest work ability’ [19, 20]. This single question has previously been shown to adequately assess the status and progress of work ability [20].

*General health* will be measured using two selected items from the SF-36 Health Survey concerning self-perceived general health (at present and one year ago) “In general, would you say your health is” and “Compared to one year ago, how would you rate your health in general now?” Answers will be recorded using a 5-point Likert Scale ranging from excellent to poor and from much better now than one year ago to much worse than one year ago [21, 22].

Five components of *physical fitness* will be evaluated using a numeric rating scale with illustrations and verbal anchors for the extremes. There is one question and it relates to each of the five components: aerobic fitness, muscle strength, endurance, flexibility and balance. “How would you rate the following components of physical fitness compared with others of your own age and sex?”. Answers will be recorded on an 11-point numeric scale ranging from weak to strong or poor to good [23, 24]. The questions have been translated into Danish and validated [23].

*Physical activity* will be measured with a single question “This question is about how much you move and exert yourself physically during your leisure time?” from the Saltin-Grimby Physical Activity Level Scale. The answer is recorded on a 4-point Likert scale measuring a range from almost completely passive to strenuously active [25–27].

*Pain* will be measured on a Visual Analogue Scale (VAS) using a 100 mm VAS anchored with ‘no pain’ at 0 mm and ‘worst imaginable pain’ at 100 mm during the last 7 days [28].

#### The psychological domain

*Well-being* will be measured using the WHO-5 Well-Being Index [29, 30] which is a questionnaire that measures current mental well-being. It is a 5-item questionnaire originally developed from the 28-item WHO Well-Being Questionnaire and it has been shown to have both clinical and psychometric validity [31].

*Depression and anxiety* will be measured using the Patient Health Questionnaire-4 for Depression and Anxiety (PHQ-4). It is an ultra-brief screening instrument consisting of four items, which includes two validated two-item screeners (PHQ-2 and GAD-2). Answers will be measured on a 4-point Likert scale measuring a range from ‘not at all’ to ‘nearly every day’ [32, 33].

*Loneliness* will be measured using the *T-ILS* [34] for loneliness. It is a short version of the longer UCLA version and it consists of three items which have shown adequately agreement with the UCLA version to assess loneliness [35, 36]*.* Answers will be measured on a 3-point Likert scale measuring the range ‘Hardly ever’, ‘Some of the time’ and ‘often’.

*Self-efficacy* will be measured using the 10-item psychometric scale ‘The General Self-Efficacy Scale’ [37] which is designed to assess the belief in one’s competence to cope with a broad range of stressful or difficult demands in life [38]. Answers will be measured at a 4-point Likert Scale ranging from ‘not at all true’ to ‘exactly true’ [29, 37, 39].

*Kinesiophobia* refers to dysfunctional beliefs about physical activity, and it has been conceptualized as a fear of movement or (re)injury by Vlaeyen et al. [40]. Pain-related fear has previously been shown to be a valid predictor of chronic pain and disability [41]. Kinesiophobia will be measured using the Tampa Scale for Kinesiophobia [42–44]. The scale consists of 17 items each of which can be answered on a 4-point Likert Scale ranging from strongly agree to strongly disagree [45].

